### 2.7. Data Collection and Quality Control

A series of standard operating procedures will be established for data collection and quality control in the trial. Investigators and research assistants will receive a minimum of 4 hours training on study procedures prior to the enrollment. Detailed descriptions of the data collection schedule are provided in Table 3. Clinical data will be collected by a case report form (CRF) and then be transcribed into an electronic data capture (EDC) system developed by IBRCM. With EDC's consistency checking program and manual verification, all participant data will undergo validation checks for completeness, accuracy, and consistency.

The site principal investigator will oversee and be responsible for data collection, recording, and quality. The safety, integrity, and conduct of the trial will be monitored by an independent DSMB consisting of seven independent members. Besides, data monitoring will be entrusted to the Beijing Yaohai Ningkang Pharmaceutical Technology Co. Ltd. The auditing of the trial will be conducted by the Scientific Research Department at the Guangdong Provincial Hospital of Chinese Medicine, as well as the Office of the National Key Research and Development Program of China.

### 2.8. Statistical Analysis

#### 2.8.1. Sample Size Calculation

Sample size calculation of this trial consists of two parts: the RCTs and the observational study. Firstly, the sample size of each RCT was estimated, and the detailed estimation process can be found in subtrial protocols [25, 26]. In brief, a total of 430 patients diagnosed with dampness pattern (218 AD patients and 212 IBS-D patients) will be enrolled in the RCTs. Secondly, we assumed that the prevalence of dampness pattern is 39% in the AD population and is 81% within the IBS-D based on previous studies [33, 34]. Thus, 560 patients are required for the AD cohort and 270 for the IBS-D cohort. Considering a 15% loss to follow-up rate, the total sample size of cohorts is adjusted to 1000. Therefore, 570 patients diagnosed with nondampness pattern are required in the observational studies (as shown in Table 1).

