### 2.2. Study Design and Setting

This master protocol consists of two multicenter, double-blinded, randomized placebo-controlled trials and a real-world observational study (Table 1): the CHARM trial (the Chinese herbal formula Huoxiang Zhengqi for atopic dermatitis with dampness pattern) [25] and the CHAIRS trial (the Chinese herbal formula Huoxiang Zhengqi for diarrhea-predominant irritable bowel syndrome) [26]. At the beginning of this trial, two registry-based cohorts of AD and IBS-D will be established, where patients with dampness pattern will be enrolled in the RCTs, and patients with nondampness pattern will be retained in the cohort constituting a real-world observational study. Thus, dampness pattern will be contrasted with nondampness pattern.

A total of 678 AD patients and 322 IBS-D patients will be enrolled from 14 hospitals in China over a 3-year period. Patients in the RCTs will be randomized at a ratio of 1 : 1 to receive either HXZQ oral liquid or a placebo for 4 weeks and then be followed up for another 4 weeks, while patients in the observational study will experience a 12-week follow-up.  Figure 1 displays the study flowchart. This study has been approved by the Ethics Committees of each participating site. Substudies have been registered in the Chinese Clinical Trial Registry (ChiCTR1900026700 and ChiCTR1900026837). An independent data safety monitoring board (DSMB) will monitor the overall conduct of the trial and assess the safety and efficacy of study procedures.

CHARM, Chinese herbal formula Huoxiang Zhengqi for atopic dermatitis with dampness pattern; CHAIRS, Chinese herbal formula Huoxiang Zhengqi for diarrhea-predominant irritable bowel syndrome; AD, atopic dermatitis; IBS-D, diarrhea-predominant irritable bowel syndrome; HXZQ, Huoxiang Zhengqi oral liquid.

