### 2.3. Participants

#### 2.3.1. Recruitment

Participants will be recruited via posters in hospitals and advertisements in social media. To ensure a feasible and efficient recruitment, two registry-based cohorts will be established at the beginning of this trial. Based on predefined diagnostic criteria [6, 27], patients who present to a participating clinical site for treatment of AD will be screened for the AD cohort, and patients with IBS-D will be screened for the IBS-D cohort. In this registry period, broad eligibility criteria will be used to expedite the screening process. Then, eligible patients in the cohorts will further be classified as either “the dampness pattern” or “the nondampness pattern” following CM pattern differentiation. Subsequently, patients with dampness pattern will enter one of the RCTs, while patients with nondampness pattern will participate in the observational study. To be eligible for the RCTs, patients must again be screened against the specific inclusion and exclusion criteria (Table 2). Screening and enrollment logs will record enrolled patients, the reasons for exclusion, and the reasons eligible patients who are not enrolled.

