## Figures and Tables

**Figure 1 fig1:**
[figure not shown]
Study flowchart. AD, atopic dermatitis; IBS-D, diarrhea-predominant irritable bowel syndrome; HXZQ, Huoxiang Zhengqi oral liquid.

**Table 1 tab1:** Summary of study populations and intervention.

Trial name	Study design	Population	Intervention	Sample size
CHARM	RCT	AD with dampness pattern	HXZQ oral liquid vs. placebo	218
CHAIRS	RCT	IBS-D with dampness pattern	HXZQ oral liquid vs. placebo	212
—	Observational study	AD with nondampness pattern	—	460
		IBS-D with nondampness pattern		110

**Table 2 tab2:** Inclusion and exclusion criteria for patient selection in the RCTs.

Inclusion criteria	Exclusion criteria
Patients who meet all of the following criteria are eligible for the RCTs:	Patients who meet any of the following criteria are not eligible to participate in the RCTs:
1. Patients between 18 and 70 years of age and informed consent obtained	1. Patients with any uncontrolled cardiovascular, respiratory, digestive, urinary, or hematological disease; known cancer or mental illness
2. Diagnosed with CM dampness pattern	2. Examination results show ALT or AST levels exceeding 2 times the upper limit normal value; or BUN level exceeds 1.5 times the upper limit normal value during the screening period
3. CHARM (a) 1% < body surface area (BSA) < 10% (b) 1 ≤ investigator's global assessment (IGA) ≤ 3	3. Anyone allergic to any medicine or ingredients used in the study
	4. Women who are pregnant or lactating or plan to become pregnant in three months
4. CHAIRS (a) Initial irritable bowel syndromes symptom severity (IBS-SSS) score >75 (b) Patients had to be literate	5. Those who are considered unfit for the trial
	6. CHARM (a) those who have ever used HXZQ for treating eczema (b) medication used: systemic therapy with immunomodulatory or immunosuppressive agents (including tripterygium wilfordii) within the previous 4 weeks; topical or systematic therapy with antibiotics or antihistamines within the previous 2 weeks phototherapy (such as PUVA, UVA, or UVB) within the previous 4 weeks; topical therapy with immunomodulator within the previous 2 weeks; or topical or systematic use of any over-the-counter drugs within the previous week (c) those who are participating in any other clinical trial or had participated in a clinical trial within the previous month

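### The cohort sizing allows nothing for the second RCT eligibility screen, and Table 1's split of 678 AD and 322 IBS-D patients does not fit the stated 39% and 81% dampness prevalences

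*Protocol article*

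**What the plan says.** All references are to the protocol article.

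- **RCT sizes (2.8.1).** The starting point is that "a total of 430 patients diagnosed with dampness pattern (218 AD patients and 212 IBS-D patients) will be enrolled in the RCTs". The derivation of these two numbers is referred to the subtrial protocols, which are not shown.
- **Prevalence (2.8.1).** The article states: "we assumed that the prevalence of dampness pattern is 39% in the AD population and is 81% within the IBS-D based on previous studies".
- **Cohort sizes (2.8.1).** From these two inputs it concludes: "Thus, 560 patients are required for the AD cohort and 270 for the IBS-D cohort".
- **Inflation (2.8.1).** "Considering a 15% loss to follow-up rate, the total sample size of cohorts is adjusted to 1000". Section 2.2 gives the split by disease: "A total of 678 AD patients and 322 IBS-D patients will be enrolled from 14 hospitals in China over a 3-year period".
- **Observational groups (2.8.1, Table 1).** "Therefore, 570 patients diagnosed with nondampness pattern are required in the observational studies". Table 1 shows 460 in the row "AD with nondampness pattern" and 110 in the matching IBS-D row.
- **Second screen (2.3.1, Table 2).** Cohort entry uses broad criteria. Before entering an RCT, "patients must again be screened against the specific inclusion and exclusion criteria". Table 2 adds limits that the cohort criteria in 2.3.2 and 2.3.3 do not contain: body surface area and IGA ranges, earlier HXZQ use and drug washouts for CHARM; IBS-SSS, literacy, warning signs, abdominal surgery and anxiety and depression scores for CHAIRS; liver and renal limits for both.

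**The concern.** The path from cohort to RCT has two steps, pattern classification and then the Table 2 screen, but the sizing contains only the first. Table 1 has the same gap: its rows are dampness patients in an RCT and nondampness patients in the observational study. A patient with dampness pattern who fails the screen or declines randomisation fits neither row.

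Three things depend on this. The first is how many patients must be registered to fill the RCTs, which carry the primary objective. The second is the size of the observational groups, on which the propensity-score comparisons in 2.8.2 rely. The third is who counts as a dampness patient in the planned comparisons of dampness with nondampness, items (3) to (5) of the overall analysis in 2.8.2.

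**Working it through.** **Inputs.** RCT sizes 218 (AD) and 212 (IBS-D), prevalences 0.39 and 0.81, interim cohorts 560 and 270, and the 15% allowance are from 2.8.1. Final cohorts 678 and 322 are from 2.2. Observational sizes 460 and 110 are from Table 1.

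**Step 1: reproduce the plan's figures.** Cohort = RCT size / prevalence.
- AD: 218 / 0.39 = 559 (stated 560).
- IBS-D: 212 / 0.81 = 262 (stated 270, so 8 to spare).
- Inflation: (560 + 270) / 0.85 = 977, which the article carries to 1000.

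The figures reproduce to within rounding, and the formula has no term for screen failure or refusal.

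**Step 2: where the inflation goes.** AD rises by 678 − 560 = 118, and IBS-D by 322 − 270 = 52. Before inflation the nondampness remainder is 560 − 218 = 342 and 270 − 212 = 58. Then 342 + 118 = 460 and 58 + 52 = 110, exactly Table 1. The whole increase is counted as nondampness.

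**Step 3: apply the plan's own prevalences to its final cohorts.**

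| | AD (678) | IBS-D (322) |
|---|---|---|
| Expected dampness | 678 × 0.39 = 264.4 | 322 × 0.81 = 260.8 |
| Dampness in Table 1 (RCT only) | 218 | 212 |
| Dampness with no row | 46.4 | 48.8 |
| Expected nondampness | 678 × 0.61 = 413.6 | 322 × 0.19 = 61.2 |
| Nondampness in Table 1 | 460 | 110 |
| Excess in Table 1 | 46.4 | 48.8 |
| Dampness share implied by Table 1 | 218 / 678 = 32.2% | 212 / 322 = 65.8% |

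This step needs no outside assumption.

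**Step 4: pass rate needed to fill the RCTs.** Required fraction = RCT size / expected dampness patients.
- At 678 and 322: 218 / 264.4 = 82.4% and 212 / 260.8 = 81.3%.
- At the interim 560 and 270: 218 / (560 × 0.39) = 99.8% and 212 / (270 × 0.81) = 96.9%.

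**Step 5: cohort size with the missing term.** Cohort = RCT size / (prevalence × fraction). The article does not give the fraction, so the values below are assumptions.

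| Assumed fraction | AD, before / after 15% | IBS-D, before / after 15% |
|---|---|---|
| 100% | 559 / 658 | 262 / 308 |
| 90% | 622 / 731 | 291 / 343 |
| 80% | 699 / 823 | 328 / 385 |
| 70% | 799 / 940 | 374 / 440 |

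**The case against.** **The stated numbers do work on the stated inputs.** 560 × 0.39 = 218.4 and 270 × 0.81 = 218.7. A reader might infer that the cohorts cannot deliver 218 and 212, but the documents do not support that. The 560 and 270 are interim figures, and the cohorts to be enrolled are 678 and 322. Shortfall appears only below a pass rate of about 81 to 82%, and the article gives no pass rate. This stands.

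**The 15% margin can absorb screen failures.** Table 3 puts consent, pattern differentiation and randomisation all at baseline, so follow-up loss comes after randomisation and does not reduce the number randomised. This stands too, and it is why 82.4% and 81.3% are the relevant thresholds. But 2.8.1 labels the margin as loss to follow-up and Table 1 allots it to nondampness patients, so it is not planned for screening.

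**No power loss follows.** A reader might go on to infer an underpowered RCT. That would need a planned power, a pass rate and a rule that recruitment stops at the cohort total with the RCTs unfilled. The article states none of these. It gives 218 and 212 as RCT sizes, and their derivation is in documents not shown.

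**Table 1 need not list screen failures.** The 678 and 322 might count only patients placed in a substudy, with the rest in the screening logs of 2.3.1. Then 460 and 110 nondampness patients imply 460 / 0.61 = 754 AD and 110 / 0.19 = 579 IBS-D patients classified. These include 294 and 469 with dampness, and implied pass rates of 218 / 294 = 74% and 212 / 469 = 45%. The article states neither these rates nor a cohort of 754 + 579 = 1333, and 2.8.1 calls 1000 the total size of the cohorts. So this reading does not reconcile the figures either.

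**Conclusion.** The point holds as a gap and an inconsistency in the cohort sizing. Section 2.8.1 has no term for the screen that 2.3.1 and Table 2 require. Table 1's split also cannot hold together with the stated prevalences: about 46 AD and 49 IBS-D dampness patients have no place, and the observational groups are overstated by the same numbers. The effect is largest in IBS-D, where about 61 nondampness patients are expected against 110 stated. On the article's own figures it is the observational groups that fall short.

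Whether the RCTs fill within 678 and 322 is open, because it depends on an eligible-and-consenting fraction that is not stated. The conclusion takes the 39% and 81% as given and reads 678 and 322 as cohort totals, as 2.8.1 does.

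**What to change.** Restate 2.8.1 and Table 1 as follows.

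- Say that 218 and 212 randomised patients are the governing recruitment targets.
- Describe 560 and 270 as minimums at 100% eligibility, before inflation.
- Give each cohort total as RCT size / (prevalence × eligible-and-consenting fraction), with a stated range for the fraction and the 15% allowance shown separately. Update the fraction from the screening logs already planned in 2.3.1.
- Add a Table 1 row for dampness patients who are not randomised.
- Reconcile 460 and 110 with the 39% and 81% prevalences (about 414 and 61 at cohorts of 678 and 322).

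The cost is a restatement of text and one table, and the RCT targets do not change. The downside is that the cohort and observational totals become expected ranges rather than fixed numbers, and at a cohort of 322 the stated IBS-D nondampness number becomes smaller.

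### The nondampness sample sizes (570 in total; 460 AD and 110 IBS-D in Table 1) do not follow from the protocol's own dampness prevalences, which give about 475 (414 and 61)

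*Protocol article*

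**What the plan says.** Section 2.8.1 builds the sample size in a chain.

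- It starts from the trials: "a total of 430 patients diagnosed with dampness pattern (218 AD patients and 212 IBS-D patients) will be enrolled in the RCTs".
- It takes a prevalence for each disease: "we assumed that the prevalence of dampness pattern is 39% in the AD population and is 81% within the IBS-D".
- From these come the cohorts before loss: "560 patients are required for the AD cohort and 270 for the IBS-D cohort".
- It then allows for loss: "Considering a 15% loss to follow-up rate, the total sample size of cohorts is adjusted to 1000".
- It concludes that "570 patients diagnosed with nondampness pattern are required in the observational studies", and refers to Table 1.

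Section 2.2 splits the total by disease: "A total of 678 AD patients and 322 IBS-D patients will be enrolled from 14 hospitals in China over a 3-year period". Table 1 gives 460 for AD without dampness pattern and 110 for the row labelled "IBS-D with nondampness pattern". Section 2.3.1 sends cohort patients with dampness pattern to the RCTs, after a second eligibility screen, and the others to the observational study.

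**The concern.** The prevalences are used to size the cohorts and then dropped when the cohorts are divided into their two parts. If 81% of IBS-D patients have dampness pattern, 19% do not. Yet 110 of 322 is 34%.

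The number matters because the nondampness patients carry three things in Section 2.8.2: the AD and IBS-D contrasts of dampness against nondampness (items 3 and 4 of the overall analysis), the pooled contrast (item 5), and the propensity score matching between medication groups. The matching subdivides the nondampness patients of each disease further. If the IBS-D group is much smaller than Table 1 says, those analyses are thinner than the reader is led to expect, or more patients must be screened than the protocol plans for.

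**Working it through.** **Inputs.** From Section 2.8.1: RCT counts 218 (AD) and 212 (IBS-D); dampness prevalence 39% and 81%; cohorts before loss 560 and 270; loss 15%; total 1000; nondampness total 570. From Section 2.2: final cohorts 678 and 322. From Table 1: nondampness 460 and 110.

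**1. Cohorts before loss** (RCT count / dampness prevalence).
- AD: 218 / 0.39 = 559.0; stated 560.
- IBS-D: 212 / 0.81 = 261.7, or 262; stated 270.

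Rounding up to the next ten gives both stated figures.

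**2. Loss allowance** (N / (1 - 0.15)).
- AD: 560 / 0.85 = 659; stated 678.
- IBS-D: 270 / 0.85 = 318; stated 322.
- Total: 830 / 0.85 = 977; stated 1000.

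Each stated figure lies above the computed one, by less than 3%. Up to here the chain holds, with loose rounding.

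**3. How the plan's nondampness figures arise.**
- 678 - 218 = 460
- 322 - 212 = 110
- 1000 - 430 = 570

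The match is exact. The cohorts have been inflated for loss and the RCT counts have not. Before inflation the remainders were 560 - 218 = 342 and 270 - 212 = 58. The inflation adds 678 - 560 = 118 and 322 - 270 = 52 patients, and 342 + 118 = 460, 58 + 52 = 110. All 170 added patients are treated as nondampness, although at the assumed prevalences 39% of the added AD patients and 81% of the added IBS-D patients would have dampness pattern.

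**4. What the stated prevalences give** (final cohort x (1 - prevalence)).

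| | Final cohort | Nondampness share | Expected | Stated | Shortfall |
|---|---|---|---|---|---|
| AD | 678 | 0.61 | 413.6 (414) | 460 | 46 (10%) |
| IBS-D | 322 | 0.19 | 61.2 (61) | 110 | 49 (45%) |
| Total | 1000 | | 474.8 (475) | 570 | 95 (17%) |

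The other side of the ledger agrees. Expected dampness patients are 678 x 0.39 = 264 and 322 x 0.81 = 261. These exceed the RCT counts by 46 and 49, the same 95 patients.

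**5. Prevalence implied by Table 1.** 218 / 678 = 32% for AD and 212 / 322 = 66% for IBS-D, against 39% and 81%.

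**6. Alternatives that might rescue the figures.**
- Inflating only the nondampness remainder: 342 / 0.85 = 402 and 58 / 0.85 = 68. Neither matches.
- Chance: if 322 patients are classified and 19% are nondampness, the exact binomial probability of 110 or more is about 1e-10. For 460 or more of 678 at 61% it is about 1e-4.

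**7. Patients needed to fill 460 and 110 at the stated prevalences.** 460 / 0.61 = 754 AD and 110 / 0.19 = 579 IBS-D, together 1,333.

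**The case against.** The best defence is that 678 and 322 are enrolment totals, not the number of patients classified. The text nowhere says that enrolment is consecutive, and Section 2.3.1 provides for logging eligible patients who are not enrolled. On that reading, 212 trial patients and 110 observational patients are two quotas that sum to 322, and more patients are screened to fill them. This has some force: 110 is not impossible, and the binomial probability above applies only if 322 is the whole classified cohort. But no quota is stated. Section 2.8.1 calls 1000 the size of the cohorts, derives the cohorts from prevalence, and presents 570 as a consequence. Failures at the second RCT screen do not help either, because under Section 2.3.4 pattern is assigned by symptoms, so a dampness patient who fails that screen is still a dampness patient.

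It can also be said that the observational analyses are described as exploratory and have no stated power or precision target, so no target is missed. That is right, and it limits the weight of the point.

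Two stronger readings are tempting and should not be drawn.
- A reader might infer that 270 was obtained from the wrong trial's count, since 218 / 0.81 = 269.1. But 212 / 0.81 = 262 rounded up to the next ten is also 270, and the same rule turns 559 into 560. The number cannot show which count was used.
- A reader might infer that 1000, 678 and 322 are miscalculated because 15% loss gives 977, 659 and 318. The differences are under 3% and all upward; this is generous rounding.

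**Conclusion.** The point stands for the last step of Section 2.8.1 and for the observational rows of Table 1, and only there. With the protocol's prevalences and its final cohorts, the observational study would have about 414 AD and 61 IBS-D patients, 475 in all, not 460, 110 and 570. The IBS-D group is hit hardest, at about 45% below the stated size.

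This rests on two assumptions: that 39% and 81% are right, and that 678 and 322 are the patients classified by pattern. If the true prevalences were near 32% and 66%, Table 1 could be met, but those are not the values the protocol adopts.

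The error affects the exploratory observational part alone. The 218 and 212 are inputs here; they are derived in subtrial protocols that are not shown, and nothing in this point touches them.

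**What to change.** Choose one of two restatements in Section 2.8.1 and Table 1.

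1. Keep 678 and 322. Replace 570 by about 475, and the Table 1 rows by about 414 AD and 61 IBS-D. Section 2.2 and the abstract need no change on this account, since they give only 678 and 322.
2. Keep 460 and 110. State that they are recruitment quotas, and that filling them at the assumed prevalences means screening and classifying about 754 AD and 579 IBS-D patients. At those numbers about 294 AD and 469 IBS-D patients would have dampness pattern (754 x 0.39 and 579 x 0.81), which is 76 and 257 more than the RCTs take. The text should say what happens to these 333.

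Under either option, bring the flowchart into line if it shows these counts. The figures 560, 270 and 1000 can stay.

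The first option costs a few edited numbers and a less favourable stated size for the IBS-D observational group. The second costs additional screening.

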#### 2.8.2. Statistical Methods

A statistical analysis plan (SAP) will be developed prior to the completion of the trial. All data will be analyzed by statisticians using SPSS 18.0 (IBM SPSS Inc., Armonk, New York, USA) and SAS 9.2 (SAS Institute Inc., Cary, USA), and two-sided *P* values <0.05 are considered statistically significant.

First, the analysis will be undertaken independently for each RCT [25, 26]. Baseline characteristics will be summarized using descriptive statistics and will be listed by groups. Efficacy analysis will be performed in both intention-to-treat (ITT) and per-protocol (PP) populations. Missing data will be processed with the multiple imputation method, and if necessary, sensitivity analysis will be used to explore the robustness of the results. For all outcomes, *t*-test or Mann–Whitney *U* test will be employed for continuous variables; Chi-squared test or Fisher's exact test will be used for categorical variables. The changes across time among outcomes will be analyzed by repeated measure analysis of variance. Center effect and other factors based on professional judgement like gender, age, and disease course will be adjusted by logistic regression model or Cox regression model. For safety assessments, comparisons of the incidence and severity of AEs or adverse drug reactions (ADRs) between the groups will be performed by Chi-square test, Fisher's exact test, or Wilcoxon rank-sum tests based on the data characteristics. Occurrences of AEs will be listed in a summary table containing the time of occurrence, severity, duration, adopted measures, causality assessment, and prognosis.

Second, the analysis of the observational study will be conducted for each of the two disease (AD and IBS-D) populations. To investigate the real-world based effectiveness in this part, some exploratory analysis methods will be adopted [35]. Briefly, baseline characteristics of these nondampness pattern patients will be described using univariate analysis to profile the general demographics, disease features, and medication uses for each disease group. Then, all outcomes will be analyzed and compared between different medication groups by propensity score matching (PSM). Safety assessments of observational part will follow the same procedures and methods as those in the RCTs.

Finally, an overall analysis will be performed combining multiple subgroups to comprehensively investigate the effect of HXZQ for dampness pattern. These subgroups analyses will include (1) HXZQ vs. placebo for AD patients, (2) HXZQ vs. placebo for IBS-D patients, (3) AD patients with dampness pattern vs. AD patients without dampness pattern, (4) IBS-D patients with dampness pattern vs. IBS-D patients without dampness pattern, and (5) patients with dampness pattern vs. patients without dampness pattern. We will pay special attention to the analysis of CM pattern, including the clinical manifestations, tongue and pulse signs, and pattern diagnosis. Based on the time sequence of clinical symptoms and CM pattern transition at each visit, a Markov model will be constructed to describe the changes of CM pattern over time [36]. The influence of interventions and related covariates (gender, age, disease, condition, CM pattern, etc.) on this change process will also be detected using mixed-effects models, or multilevel models. Then, to identify whether there are common or disease-specific changes of dampness pattern in different diseases, we will compare the dampness pattern changes of AD and IBS-D patients. Furthermore, the correlation of CM pattern and disease outcomes will be analyzed. Several methods such as logistic regression model, Cox regression model, and Bayesian hierarchical model will be explored and compared to establish a reasonable and accurate disease prognosis predictive model based on CM pattern [35].

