#### 2.4.3. Randomization and Blinding

Eligible patients in each RCT will be equally randomized to receive either HXZQ oral liquid or placebo through an interactive web response system. A center-stratified random sequence will be created with SAS 9.2 (SAS Institute Inc., Cary, USA). The randomization will be independently performed and managed by the Institute of Basic Research in Clinical Medicine (IBRCM), China Academy of Chinese Medical Sciences (Beijing, China). Patients and researchers involved in the trial including clinicians, research assistants, outcome assessors, and statisticians will be blinded to treatment allocation. In the observational study part, patients will receive no experimental interventions of this study. Investigators will just document the medical records, and blinding is not required.

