### 2.5. Outcome Measurements

#### 2.5.1. Primary Outcome

For all AD patients, the primary outcome is the change in the Eczema Area and Severity Index (EASI) scores from baseline to the end of treatment (4^th^ week). EASI is the core outcome measurement instrument for AD, and the higher the score is, the more severe the AD is [29]. For IBS-D patients, the proportion of responders for adequate relief (AR) is the primary outcome evaluating the degree of symptom alleviation [30]. Throughout the study, IBS-D patients will be weekly asked the question: “Has your irritable bowel syndrome pain and discomfort adequately relieved in the past week?” (yes/no). Responders are defined as those who answer “yes” for at least 50% of the time, for example, in the RCT, that is, 2 out of 4 weeks in the treatment period. The proportion will be separately analyzed in the treatment period and the follow-up period.

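### Repeated-measures ANOVA is named for change over time without limit to continuous outcomes, and no stated model gives a baseline- and centre-adjusted week-4 estimate for the continuous ones

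*Protocol article*

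**What the plan says.** Section 2.8.2 of the protocol article describes the RCT analysis in layers.

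- **Two-group comparisons.** A t-test or Mann–Whitney U "test will be employed for continuous variables", and "Chi-squared test or Fisher's exact test will be used for categorical variables". Two-sided P "values <0.05 are considered statistically significant".
- **Time course.** "The changes across time among outcomes will be analyzed by repeated measure analysis of variance". No outcome type is excluded, and no model term or set of visits is named.
- **Adjustment.** Centre and factors such as gender, age and disease course are handled by logistic or Cox regression.
- **Missing data.** "Missing data will be processed with the multiple imputation method".

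Treatment is given "for 4 weeks and then be followed up for another 4 weeks" (section 2.2). Table 3 places the RCT visits at weeks 0, 2, 4 and 8 for AD and at weeks 0, 4 and 8 for IBS-D, so week 8 is off treatment.

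Section 2.5.1 sets the AD primary outcome as EASI change to week 4. The IBS-D primary outcome is a responder proportion: "Throughout the study, IBS-D patients will be weekly asked the question", with yes/no answers, and the proportion is analysed separately for the treatment and follow-up periods. Section 2.5.2 adds EASI-50, EASI-75 and IGA for AD.

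**The concern.** The time-course sentence names a method, so its scope can be judged on the text. It has two weaknesses.

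First, the sentence before it separates continuous from categorical variables, but this one does not. Several repeatedly measured outcomes are binary or ordinal, and a normal-theory ANOVA is a poor model for them whichever term is tested.

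Second, the clinically relevant time point is week 4. If every scheduled visit enters the ANOVA, its usual outputs do not estimate the week-4 difference. The adjustment sentence does not fill that gap, because logistic regression needs a binary response and Cox regression a time to event. The trial would then report continuous outcomes with unadjusted two-group tests and a time-course test that is hard to interpret, but with no visit-specific estimate adjusted for baseline and for centre, the randomisation stratum.

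**Working it through.** The plan states no figure for this point, so there is none to reproduce. Effect size, SD and power for the RCTs are left to the subtrial protocols.

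**Step 1: outcome types against the method**

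| Outcome | Type | RCT schedule | Suited to repeated-measures ANOVA? |
|---|---|---|---|
| EASI, Skindex-29 | continuous | weeks 0, 2, 4, 8 | in type, yes |
| IBS-SSS, IBS-QOL | continuous | weeks 0, 4, 8 | in type, yes |
| IGA | ordinal; 1 to 3 at entry (Table 2) | weeks 0, 2, 4, 8 | no |
| EASI-50, EASI-75 | binary | weeks 2, 4, 8 | no |
| Adequate-relief answers | binary | weekly | no, if modelled over time |

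For a binary outcome the variance is p(1 − p), so it changes as response changes. With assumed response of 10%, 30% and 50%, it is 0.09, 0.21 and 0.25.

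**Step 2: what the group main effect estimates**

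With baseline as one of the levels, the main effect is the mean of the visit differences. Randomisation makes the expected baseline difference zero. Set the week-4 effect to 1 and assume half of it at week 2.

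- AD, week-8 effect full: (0 + 0.5 + 1 + 1)/4 = 0.625
- AD, half: (0 + 0.5 + 1 + 0.5)/4 = 0.50
- AD, nil: (0 + 0.5 + 1 + 0)/4 = 0.375
- IBS-D, full: (0 + 1 + 1)/3 = 0.67
- IBS-D, half: (0 + 1 + 0.5)/3 = 0.50
- IBS-D, nil: (0 + 1 + 0)/3 = 0.33

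If the AD effect were already full at week 2 and stayed full, the value would be 3/4 = 0.75. It is below 1 in every case here.

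**Step 3: what group-by-time tests**

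It has (visits − 1) degrees of freedom: 3 for AD and 2 for IBS-D. It is not diluted by baseline. It asks whether the arm difference varies over any visits, week 8 included, and returns no week-4 estimate.

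**Step 4: illustrative power**

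Inputs from the article: 218 AD and 212 IBS-D patients, and "Eligible patients in each RCT will be equally randomized", so n = 109 and 106 per arm; two-sided 0.05. Assumptions: SD 1, equal correlation ρ between visits, complete data, and a week-4 effect d that gives the change-score t-test 80% power.

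- t-type analyses: noncentrality = d/√(2v/n), with v = 2(1 − ρ) for change and v = 1 − ρ² for baseline-adjusted week 4.
- Group main effect over k visits: the mean effect replaces d, and v = (1 + (k − 1)ρ)/k.
- Group-by-time: F noncentrality = (n/2) × Σ(effect − mean effect)²/(1 − ρ).

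Baseline-adjusted analysis for AD:

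| ρ | d | Change t-test | Baseline-adjusted week 4 |
|---|---|---|---|
| 0.3 | 0.451 | 80% | 94% |
| 0.5 | 0.381 | 80% | 90% |
| 0.7 | 0.295 | 80% | 86% |

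For example, at ρ = 0.5 the change noncentrality is 0.381/√(2 × 1/109) = 2.81. The adjusted one is 0.381/√(2 × 0.75/109) = 3.25.

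Repeated-measures ANOVA at ρ = 0.5, for a full, half or nil week-8 effect:

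- AD: main effect 60%, 43%, 26%; group-by-time 80%, 65%, 80%.
- IBS-D, continuous scale: main effect 63%, 40%, 21%; group-by-time 83%, 71%, 83%.

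Over ρ from 0.3 to 0.7 and these profiles, main-effect power runs from 85% down to 15% (AD) and from 86% down to 13% (IBS-D).

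**The case against.** The strongest reply is that repeated-measures ANOVA is supplementary. A reader might infer that the week-4 primary effect will be missed or blurred. The documents do not support that. The AD primary outcome is fixed as a change to week 4, and two-group comparisons go to the t-test or Mann–Whitney U, which use neither averaging over visits nor week-8 data. Adequate relief is already split by period. This stands, and it limits the point to the time-course and adjusted analyses.

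Other strong readings also fail:

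- **That the method governs all outcomes.** Those words open the sentence on two-group tests, and section 2.8.2 gives CM pattern its own Markov and mixed-effects or multilevel models.
- **That dilution is certain.** It follows only if the group main effect including baseline is used, and the article names no term.
- **That power must fall.** At ρ = 0.3 with a sustained effect, the main effect beats the change t-test (85% against 80% in AD).
- **That the false-positive rate is inflated by non-sphericity.** The article does not say that the test would go uncorrected.

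It can also be said that terms, visits and corrections belong in the SAP or the subtrial protocols. That is fair for omitted detail. It does not answer a named method whose wording covers outcomes it does not fit, or named adjustment models that cannot take a continuous response.

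**Conclusion.** The point holds in limited form. As worded, the time-course method extends to binary and ordinal outcomes that it does not suit; this needs no numerical assumption. The same is true of the adjustment sentence, which leaves EASI, Skindex-29, IBS-SSS and IBS-QOL without a stated model for a baseline- and centre-adjusted estimate.

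The rest is conditional. If all scheduled visits enter, the group main effect estimates about 0.33 to 0.67 of the week-4 effect under the half-effect-at-week-2 assumption for AD and a week-8 effect between nil and full. Group-by-time avoids that dilution but does not estimate week 4. The 94% to 86% power of the baseline-adjusted analysis is an illustration under equal visit correlation and complete data, set against the change-score t-test and not against any figure in the article.

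The primary two-group tests remain valid. This is a change that should be made, not one on which the trial's validity depends.

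**What to change.** Replace the time-course sentence.

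- **Continuous outcomes:** a mixed model for repeated measures on the post-baseline visits, with baseline value, centre, treatment, visit, treatment-by-visit and baseline-by-visit. Report week 4 as one contrast and off-treatment week 8 as another.
- **Repeated binary and ordinal outcomes** (EASI-50, EASI-75, the weekly adequate-relief answers if modelled over time, and IGA): logistic or ordinal GEE or mixed models.
- **Adjustment sentence:** refer continuous outcomes to the mixed model in place of logistic or Cox regression.

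The two-group tests, the split of adequate relief by period and the CM pattern models can stay as they are.

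The cost is a few sentences and some programming. The models have more parameters to estimate, a small drawback at about 106 to 109 patients per arm. No new data are needed, and the article says the SAP is still to be developed, so the change can be made there.
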